**Method:**

Sixty patients with MCI and early-stage dementia will be enrolled in a crossover double-blind randomized controlled trial utilizing an integrated intervention combining conventional cognitive treatment with multifocal brain stimulation and electrophysiological recordings. A battery of standardized neuropsychological tests will be employed at several time points to monitor changes, and inferential statistics will identify the changes specifically associated with the intervention. Regression analyses will be performed to ascertain the extent to which education and cognitive reserve scores may influence intervention outcomes. Analysis of electrophysiological data will contribute characterizing responders to treatment.

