The objective of the present paper is to describe a protocol for the treatment of the cognitive and affective symptoms in MCI and dementia with several specific novel features. First, the protocol adopts multifocal stimulation of relevant brain structures thought to be involved in the genesis of the symptoms. While all previous studies focused on specific areas in the frontal and temporal cortex in separate treatment conditions, in the present project multifocal tDCS over such structures is proposed to the aim of maximizing distribution of direct current over the left fronto-temporal network (12). This specific feature follows recent studies describing a fronto-parieto-temporal network involved in cognitive (dys)functions which has been shown to be effectively modulated by brain stimulation (13, 14). Multifocal stimulation of such a network could strengthen the achievable outcomes by activating a larger scale network involved in cognitive and affective processes as compared to previous studies. Second, to address the issue of heterogeneity of stimulation effects, the proposed protocol combines electrophysiological measures (EEG) with brain stimulation (9). As shown in previous studies on healthy and brain damaged individuals, electrophysiological and neuroimaging techniques may contribute clarifying the mechanisms and brain response associated with brain stimulation (10, 15–18), also accounting for possible individual differences in response to stimulation. Crucially such integration would allow identifying good and bad responders to stimulation so to target individuals which may benefit the most from a given intervention (10). Third, this study protocol will further explore the variability in response to brain stimulation raised by previous studies, considering the relationship between some demographical and psychological factors with clinical and electrophysiological outcomes. Previous studies have shown a buffering effect of age on global cognitive response following brain stimulation interventions, with larger effects in younger populations (7), and a relevant association of cognitive functioning with cognitive reserve (and its proxies), as higher cognitive performance and better emotional response were associated with higher levels of cognitive reserve (3, 19). These variables will be embedded in the study protocol to allow a comprehensive interpretation of either positive or null effects, and to plan future research on the topic.

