To achieve these purposes the present study protocol will adopt a double-blinded sham-controlled crossover experimental design in patients with MCI and early stages of dementia, combining brain stimulation and electrophysiological recording. The primary outcomes will be global cognitive functioning, anterograde verbal episodic memory and executive functions as well as affective symptoms. Secondary outcomes will be the level of functional independence in daily living and electrophysiological measures. Based on the available literature we expected to observe an effect of brain stimulation on cognitive and affective functions (7, 11). Moreover, we expect the use of EEG recording being able to provide findings useful to distinguish good and bad responders to the treatment based on individual analysis (9, 10). Finally, we hypothesize that demographic factors can modulate the possible outcomes, thus contributing to identify the patients most suitable for such intervention (3, 7).

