### Neuropsychological assessment

2.5

A brief battery of neuropsychological tests will be used to monitor cognitive functions, affective symptoms and independence in the participants involved in the treatment (T1, T2, T3; Figure 1).

*Montreal Cognitive Assessment* [MOCA; (26)]. MOCA is a brief neuropsychological tool for screening global cognitive functioning specifically designed for MCI and early stages of dementia. The test includes 8 sub-tests assessing: executive functions, visuo-spatial abilities, naming, short-term and long-term episodic memory, attention, lexical access, abstraction, spatial and temporal orientation. The test provides a maximum score of 30; the higher the score, the higher the level of global cognitive efficiency.

*Frontal Assessment Battery* [FAB; (27)]. FAB is a screening neuropsychological battery including 6 sub-tests for evaluation of executive functioning: classification, mental flexibility, motor programming, sensibility to interference, inhibitory control and environmental autonomy. The total score is up to 18; the higher the score, the higher the level of executive functioning.

*Free and Cued Selective Reminding Test* [FCSRT; (28)]. FCSRT is designed to assess episodic memory domain. The test entails learning 12 pictorial stimuli (6 living and 6 non-living), followed by free and cued recall tasks. It assesses immediate and delayed recall, both free and cued, as well as recognition ability. The FCSRT is sensitive to memory impairments where recall does not significantly improve with cues, rendering it a valuable tool for identifying early signs of the disease. The test provides separate scores for free, cued and total *immediate* recall (maximum score 36), and scores for free, cued and total *delayed* recall (maximum score 12). For these measures the higher the scores, the higher the memory performance. Moreover, the FCRS provides a cue-sensitivity index (range 0–1) representing the extent of facilitation using the semantic cues in memory recall.

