### Sample size justification and statistics

2.8

The final sample size of 60 participants is estimated based on a sample size calculation on G*Power (v. 3.1.9.7) suggesting a sample size of at least 48 participants to compare the two groups along three-time points with an effect size = 0.25, power = 0.80, *ε* = 0.75, and a Bonferroni-adjusted *α* = 0.0125 (0.05/4 primary cognitive outcomes see below) and considering a dropout rate up to 30% from previous studies (37, 38).

Demographic data will be reported using descriptive statistics. Primary outcomes will be the measures of cognitive (MOCA, FAB, FCSRT, Stoop scores) and affective (GDS scores) functioning, while independence in daily living (ADL and IADL scores) and EEG parameters will be considered as secondary outcomes. Intention-To-Treat (ITT) analyses (39), which includes all randomized participants in the groups assigned, regardless of their adherence with the entry criteria, will be adopted. ITT analysis admits noncompliance and protocol deviations and gives an unbiased estimate of the intervention effect. Missing data will be dealt with by using a mixed-effect model approach which accommodates missing data under the missing-at-random assumption (40). To assess the effect of the intervention on multiple dependent variables simultaneously, repeated-measures analyses of variance (ANOVAs) will be conducted on the primary outcomes and secondary outcomes separately with the factors Group (G1 vs. G2) and Time (T1-T3). Moreover, multiple regression models will be used to identify the factors associated with the treatment outcome, considering gender, age, education, CRS scores, and EEG power spectrum at baseline as predictors and post intervention measures of general cognitive functioning (MOCA and FAB) and functional independence measures as criteria.

To assess possible sequence or carryover effects, an exploratory comparison of treatment effects between the two randomization arms (sham first over real vs. real first over sham) will be performed.

Statistical analysis will be performed using IBM® SPSS® Advanced Statistics and R package (R Foundation). Statistical significance will be set at *p* < 0.05.

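### The regression in 2.8 models only MOCA, FAB and functional independence, although the Background says that patient factors will be related to clinical and electrophysiological outcomes

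*Protocol article*

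**What the plan says.** **The aim.** The Background of the protocol article announces that variability in response will be explored by "considering the relationship between some demographical and psychological factors with clinical and electrophysiological outcomes". It adds that "we hypothesize that demographic factors can modulate the possible outcomes", with a view to identifying the patients best suited to the intervention. The Abstract (Method) puts it this way: "Regression analyses will be performed to ascertain the extent to which education and cognitive reserve scores may influence intervention outcomes". None of these statements limits the outcomes to particular instruments.

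**The outcomes.** The Background states: "The primary outcomes will be global cognitive functioning, anterograde verbal episodic memory and executive functions as well as affective symptoms". Section 2.8 attaches instruments to these domains. MOCA, FAB, FCSRT, Stroop and GDS are primary; ADL, IADL and EEG parameters are secondary.

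**The analysis.** Section 2.8 plans regressions to find what goes with the treatment outcome. The dependent variables of these models are fixed as "post intervention measures of general cognitive functioning (MOCA and FAB) and functional independence measures as criteria". The explanatory side is fixed too, by the words "considering gender, age, education, CRS scores, and EEG power spectrum at baseline as predictors". The ANOVAs in the same section have only the factors Group and Time.

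**The concern.** The outcomes in the aim are wider than the outcomes in the analysis. Two declared secondary outcomes, ADL and IADL, are regression criteria, while three primary instruments are not. EEG is named in the aim as something to be explained, but in 2.8 it is only something that explains.

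If 2.8 is followed as written, the trial will report nothing on how age, education or cognitive reserve relate to depression scores, to the dedicated memory test, to Stroop interference or to EEG response. If the authors notice this after the data are in, any criterion added then is open to selection. FCSRT alone yields several scores and Stroop yields two (section 2.5).

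**Working it through.** **1. Coverage.** The outcome list in 2.8 against the regression criteria in 2.8:

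| Outcome | Status in 2.8 | Regression criterion? |
|---|---|---|
| MOCA | primary | yes |
| FAB | primary | yes |
| FCSRT | primary | no |
| Stroop | primary | no |
| GDS | primary | no |
| ADL, IADL | secondary | yes |
| EEG parameters | secondary | no (baseline predictor only) |

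Two of five primary instruments are modelled and three are not. GDS is the only affective instrument, so that domain is missing entirely.

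**2. Could another analysis fill the gap?** The ANOVAs cover all these outcomes but contain no age, education, reserve or gender term. The Abstract and Background also announce that EEG will help to characterise responders. That uses EEG as a marker of response and does not relate patient factors to EEG response.

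**3. What the listed regression can show.** Its stated predictors are gender, age, education, CRS and baseline EEG power. No treatment term, real-minus-sham contrast or baseline score of the outcome is named. A coefficient for education on post-intervention MOCA then says that better-educated patients score higher afterwards, which could be true with no stimulation effect at all. This limit applies to the criteria already listed as much as to any added ones.

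**4. Cost in false positives.** With k independent tests of one predictor at 0.05 (the significance level in 2.8), the chance of at least one false positive is 1 − 0.95^k.

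- Now, k = 4 (MOCA, FAB, ADL, IADL, taken as separate models): 1 − 0.95^4 = 0.19.
- With GDS, FCSRT, Stroop and one EEG measure added, k = 8: 1 − 0.95^8 = 0.34.
- For baseline EEG power, which is left out of the EEG model, k = 7: 1 − 0.95^7 = 0.30.

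The outcomes will be correlated, so these are approximations.

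**5. Cost in power.** The documents give no modulator effect size, so the correlations below are assumptions. They are single, unadjusted correlations at n = 60. By Fisher's z, power ≈ Φ(atanh(r)·√57 − z), with z = 1.96 at two-sided 0.05 and z = 2.73 at the first Holm step for eight criteria (0.05/8).

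| Assumed r | atanh(r)·√57 | Power at 0.05 | Power at 0.05/8 |
|---|---|---|---|
| 0.25 | 1.93 | 0.49 | 0.21 |
| 0.35 | 2.76 | 0.79 | 0.51 |
| 0.45 | 3.66 | 0.96 | 0.82 |

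At the first Holm step for seven criteria (0.05/7, z = 2.69), r = 0.35 gives 0.53.

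**The case against.** **The list may not be closed.** Section 2.8 does not say that only these criteria will be used, and a fuller plan may exist. That is fair. But the article names predictors and criteria explicitly, and the named list is narrower than its own aim. This is a mismatch in stated content, not a detail left for later.

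**Making a broad aim specific is normal, and few criteria protect against chance findings.** This stands in part. A short prespecified list is defensible in a sample sized for a Group-by-Time comparison. In that case the aim should be worded to match, which is why narrowing it is offered as a full alternative.

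**No statement about modulators uses the word affective.** Correct. The Background says clinical, and its remark about emotional response and cognitive reserve describes earlier studies. Affective symptoms are nevertheless a declared primary outcome, so a reader would count them among the clinical outcomes.

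**Memory and executive function are partly covered.** This also stands. MOCA has memory and executive sub-tests, and section 2.5 says that "FAB is a screening neuropsychological battery including 6 sub-tests for evaluation of executive functioning". That 2.8 files FAB under general cognitive functioning is loose wording and changes no analysis. MOCA as described in 2.5 has no mood sub-test, so the partial cover does not reach GDS.

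**Stronger readings that do not hold.** A reader might infer that the plan tests effect modification properly for MOCA and FAB and merely omits the other outcomes, so that adding criteria would by itself show who benefits. Step 3 of the working shows otherwise. A reader might also infer that a profile built on MOCA, FAB and ADL/IADL will be presented as the profile of affective response. The Discussion speaks only of patients likely to respond to stimulation, so the documents do not support that.

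**Conclusion.** The mismatch is real and modest. Three of five primary instruments and EEG response have no model relating them to patient factors, although the Background commits to relating those factors to clinical and electrophysiological outcomes. The finding rests on reading clinical outcomes as including the declared primary ones, and on no further factor analysis existing beyond what the article describes. It does not depend on the false-positive or power figures, which only price the remedy. The primary treatment comparison is untouched, so this is an inexpensive improvement to a secondary aim and not a threat to the trial's main result.

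**What to change.** Choose one of two routes before the data are seen.

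- **Widen the analysis.** In 2.8, add as regression criteria GDS, one named FCSRT score, one named Stroop score and one named EEG change measure. Leave EEG power out of the predictors in the EEG model. Label all these models exploratory.
- **Narrow the aim.** In the Abstract and the two Background statements, restrict the aim to MOCA, FAB and functional independence.

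Under either route, if results are to be described as modulation of the treatment effect, replace each post-intervention score with a baseline-adjusted or real-versus-sham change. The real-versus-sham form is the more direct, because all participants also receive cognitive therapy throughout. Otherwise describe the results as prognostic associations.

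The cost is a few sentences and about four more regressions on tests and EEG recordings already scheduled. The price is the rise in false positives shown in the working. An exploratory label deals with it at no cost in power. A Holm correction is possible but would leave only fairly strong associations detectable.

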## Discussion

3

The present study will investigate the feasibility and efficacy of an advanced, integrated, multifocal tDCS-EEG stimulation protocol in conjunction with cognitive treatment for the management of cognitive and affective symptoms observed in MCI and early-stage dementia. The project will contribute to a substantial shift in the framework of available non-pharmacological interventions for such clinical pictures, integrating different techniques and levels of analysis in a single, comprehensive protocol. This will be achieved by four key strategies: firstly, by adopting a new multifocal protocol that allows the simultaneous stimulation of fronto-temporal regions non-invasively (12, 42); secondly, by integrating the protocol with other non-pharmacological interventions to potentially enhance the mechanisms at play; thirdly, by identifying potential electrophysiological markers to brain stimulation (10); fourthly, by exploring the factors that may modulate the response to the intervention (7). The implementation of these strategies will enable the profiling of patients who are most likely to respond to brain stimulation as a rehabilitative tool (43). In such an integrated approach, the use of brain stimulation combined with conventional cognitive therapy will allow to strengthen the plasticity-driven mechanisms associated with the behavioral treatment. Moreover, the combination in the same protocol of EEG recording will allow monitoring the brain response associated with the treatment itself. The project may provide valuable insights into the intricate changes that occur in functional brain networks during pathological ageing (44–47) and potentially effective treatment procedures.

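### The regression meant to show who responds to stimulation models post-intervention score levels, with no T1 score and no real-versus-sham term, so it finds predictors of test level rather than of response

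*Protocol article*

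**What the plan says.** Section 2.8 of the protocol article states both sides of the regression.

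- Purpose: "multiple regression models will be used to identify the factors associated with the treatment outcome".
- Predictors: "considering gender, age, education, CRS scores, and EEG power spectrum at baseline as predictors".
- Outcomes: "post intervention measures of general cognitive functioning (MOCA and FAB) and functional independence measures as criteria".

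Three other places show what the result is to be used for. The abstract says: "Regression analyses will be performed to ascertain the extent to which education and cognitive reserve scores may influence intervention outcomes". The Background says: "we hypothesize that demographic factors can modulate the possible outcomes, thus contributing to identify the patients most suitable for such intervention". The Discussion expects the project's strategies, one of which is this search for modifying factors, to "enable the profiling of patients who are most likely to respond to brain stimulation as a rehabilitative tool".

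The Background also reports from earlier work that "higher cognitive performance and better emotional response were associated with higher levels of cognitive reserve".

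On design, section 2.3 gives the full battery at T1 and repeats it at T2 and T3. Under section 2.4 every participant receives eight real and eight sham sessions, in an order set by group, with cognitive therapy throughout.

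**The concern.** A factor that identifies suitable patients must change the size of the real-versus-sham effect. The planned model contains no such effect. Its outcome is the score after treatment, and its predictors are person characteristics that are expected to go with that score whatever stimulation is given. The T1 score, which would remove most of the standing differences between people, is left out. So is any term for group, sequence or condition.

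Education and CRS could therefore appear as factors in the treatment outcome even if stimulation did nothing, or helped everyone equally. If that were reported under the stated aim, a correlate of general test level would be read as a marker of response, and later work on patient selection would build on it. This is the only model the article specifies for that aim. The EEG-based individual analysis mentioned in the Background comes with no model.

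**Working it through.** **What the plan gives.** The plan states no figure for the regression. Its only sample-size figure is 48, for the Group by Time analysis. That reproduces (power 0.816 at 48 and 0.794 at 46, assuming a correlation of 0.5 between repeated measures), but it has no bearing on this point.

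**Reading the model.** Possible meanings of the post-intervention score:

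| Time of the score | What participants have had | Real-versus-sham contrast in the model? |
|---|---|---|
| T3 | everyone: both conditions plus training | none, since all have had both |
| T2 | G1 sham only, G2 real only | a between-group contrast exists in the data, but Group is not a predictor |
| End of the real block | everyone: real plus training | none, since there is no sham comparator |

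Under every reading, the education or CRS coefficient is an association with level.

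**Size, as an illustration.** Inputs:
- n = 60 (sections 2.2 and 2.8).
- k = 8 predictors: gender, age, education, CRS and one EEG value for each of the four bands in section 2.7 (assumed summary).
- Correlation of education and of CRS with the score, r = 0.2 to 0.5 (assumed range).
- Education-CRS correlation c = 0.5 (assumed).
- Other predictors unrelated to the score (assumed).
- Stable-trait share of the score 0.7 (assumed).
- Same stimulation effect for everyone, so no effect modification.

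A hand calculation for the planned model, with score variance 1:
- Standardised coefficient of education: b = r/(1+c) = r/1.5.
- Explained variance: R² = 2r²/(1+c) = 2r²/1.5.
- Standard error: SE = √[(1−R²)/((n−k−1)(1−c²))] = √[(1−R²)/(51×0.75)] = √[(1−R²)/38.25].
- Chance of p<0.05: approximately P(Z > 2.008 − b/SE), where 2.008 is the two-sided 5% point of t on 51 degrees of freedom.

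| r | b | R² | SE | b/SE | Hand result | Simulation: education | Simulation: education or CRS |
|---|---|---|---|---|---|---|---|
| 0.2 | 0.133 | 0.053 | 0.157 | 0.85 | 12% | about 13% | about 25% |
| 0.3 | 0.200 | 0.120 | 0.152 | 1.32 | 25% | about 25% | about 47% |
| 0.4 | 0.267 | 0.213 | 0.143 | 1.86 | 44% | about 44% | about 75% |
| 0.5 | 0.333 | 0.333 | 0.132 | 2.53 | 70% | about 68% | about 95% |

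Hand calculation and simulation agree.

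When the within-person real-minus-sham difference is regressed on the predictors, education is flagged in about 5% of trials, the nominal rate. For education or CRS the nominal rate is at most 2 × 5% = 10%, which is the fair comparison for the last column.

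**Is adding T1 alone enough?** No. In a simpler simulation with education as the only predictor, regressing T3 on education and T1 still flagged education in about 11%, 16%, 28% and 46% of trials, because T1 is measured with error. The treatment contrast is needed as well.

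**The case against.** The strongest case is that this is a supplementary analysis. The treatment effect is tested by the Group by Time analysis, which uses T1 to T3 and does not depend on the regression. The abstract and Discussion describe this strand as exploring. That stands, and it limits the severity.

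Second, the flagged associations are not false positives for the literal wording of section 2.8, which speaks only of factors associated with outcome. In the illustration education really does predict the score. That also stands. The error lies in using the association to identify suitable patients or likely responders, and the Background and Discussion state exactly that use.

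Third, an article may leave detail to a fuller plan. That does not help here, because the predictors and outcomes are listed outright and the list does not fit the purpose.

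Three stronger readings are tempting but not supported:
- A reader might infer that a post-intervention score can never hold a treatment contrast, because everyone receives both conditions. That is true at T3. At T2 the groups differ in what they have received, and the fault there is that Group is not in the model.
- A reader might infer a badly overfitted model with EEG entered for every electrode and band. Section 2.7 names four bands and describes no electrode-by-electrode predictors, and how EEG is summarised can be left to the full plan.
- A reader might infer much higher flagging rates from a model with education alone. The plan specifies multiple regression, and with CRS in the model the rates for education are those in the table.

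**Conclusion.** The regression is wrong as written for its stated purpose, at moderate severity. It identifies predictors of post-treatment test level, and the article intends to read them as predictors of response to stimulation.

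That conclusion follows from the listed terms and needs no simulation. The percentages (13% to 68% for education, 25% to 95% for education or CRS) rest on the assumed correlations, the 0.7 trait share and one EEG summary per band. They show scale and do not forecast this trial. Any real prognostic association pushes the rate above 5%.

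A reader might infer that the trial's efficacy conclusion is compromised. The documents do not support this, because neither the primary analysis nor the sample size uses the regression.

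**What to change.** Replace the outcome of the regression with each participant's real-minus-sham difference (T3 minus T2 in G1, T2 minus T3 in G2), with sequence in the model. Equivalently, add treatment-by-covariate interactions for gender, age, education, CRS and baseline EEG power to a mixed model adjusted for T1 and period. Report the interaction estimates with confidence intervals as exploratory effect modification. If a model of post-intervention scores is kept, state the time point, adjust it for T1 and call it prognostic.

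The change is to analysis wording only, since T1, T2 and T3 scores are already planned for everyone. The price is precision, because interaction intervals will be wide at N=60. The within-person difference also assumes little carryover across the one-week washout. A first-period check (T2 on predictor, group and their interaction, adjusted for T1) avoids that assumption. It flagged a purely prognostic predictor in about 5% of simulated trials, but it uses less of the data.

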### Study design

2.1

The study will adopt a double-blinded crossover randomized controlled design involving two clinical centers in Italy. The whole intervention will consist of two treatment phases (sham vs. real multifocal stimulation) and multiple assessment phases (T1, T2, T3). One-week washout will be interleaved between the two treatment phases (see Figure 1).

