**Figure 1 fig1:**
[figure not shown]
Overview and schedule for the study protocol. Participants will be randomized in two groups receiving two cycles of sham/real brain stimulation (G1) or real/sham stimulation (G2) with 1-week washout combined with cognitive therapy. Each cycle will involve eight sessions (S1–S8, S9–S16) twice-weekly. Neuropsychological assessment will be performed before and after each intervention (T1–T3). ADL: Activities of Daily Living; IADL: Instrumental Activities of Daily Living. CGS: Geriatric Depression Scale; CRS: Cognitive Reserve Scale; MOCA: Montreal Cognitive Assessment; FAB: Frontal Assessment Battery; FCSRT: Free and Cued Selective Reminding Test.

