### Procedure

2.3

The participants will be initially informed about the objectives of the study in an introductory meeting involving also their family members. Following this meeting, the participants will provide their informed consent. No compensation or different treatment within the clinical institution practices will be reserved to participants included in the study. Participants will then undergo a neuropsychological battery exploring cognitive functions, affective symptoms and independence in daily living (T1). The same battery of tests will be repeated at the end of the first (T2) and of the second (T3) rehabilitation cycles. The intervention will involve two rehabilitation periods involving multifocal brain stimulation (real vs. sham with a crossover design) combined with cognitive stimulation therapy. EEG recordings with eyes-opened will be performed at the beginning and the end of each period of stimulation. The CONSORT Flow Diagram that will be ensued detailing enrolment, allocation, follow-up, and analyses is provided as Supplementary File.

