### Intervention

2.4

The intervention will consist of multifocal brain stimulation combined with cognitive training. In a cross-over design, 16 stimulation sessions (two sessions for week; freely scheduled from Monday to Friday on participants’ and institutional needs) will be delivered in two blocks (8 real and 8 sham stimulation sessions) for 10 weeks. The first and the last stimulation sessions of each block (namely sessions 1, 8, 9 and 16; Figure 1) will be preceded and followed by 5-min resting state EEG recordings with eyes-opened. Recruited participants will be randomly assigned to a “SHAM-REAL” stimulation group (G1) or a “REAL-SHAM” stimulation group (G2; Figure 1) by computer-generated random numbers; one investigator (FP) will manage generation of allocation sequence and participants’ assignment to the groups. The experimenters responsible for delivering the stimulation (LC) will be blind to the stimulation being delivered during each session. Throughout the study, all participants will undergo traditional cognitive stimulation therapy, embracing within each session paper-and-pencil and computerized activities during a face-to-face interaction with the therapist at the rehabilitation service. Activities will target memory, attention, and executive functions (24, 25); the level of difficulty will be tailored on the patients’ neuropsychological profile and progressively adjusted based on patients’ response to the treatment. Each session of cognitive training will last 40 min and will follow the brain stimulation session.

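### The planned carryover check measures twice the period effect plus carryover, so neither a positive nor a null result can be read as evidence about carryover

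*Protocol article*

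**What the plan says.** Section 2.1 of the protocol article sets out a two-period crossover: "The study will adopt a double-blinded crossover randomized controlled design involving two clinical centers in Italy". Section 2.4 has participants "randomly assigned to a “SHAM-REAL” stimulation group (G1) or a “REAL-SHAM” stimulation group (G2; Figure 1) by computer-generated random numbers". On the gap between phases, section 2.1 states: "One-week washout will be interleaved between the two treatment phases".

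The neuropsychological battery is given at T1 (before cycle 1), and section 2.3 adds: "The same battery of tests will be repeated at the end of the first (T2) and of the second (T3) rehabilitation cycles". Section 2.4 states: "Throughout the study, all participants will undergo traditional cognitive stimulation therapy".

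Section 2.8 plans repeated-measures ANOVAs with factors Group (G1, G2) and Time (T1 to T3). It then gives a separate check with a stated purpose, "To assess possible sequence or carryover effects", and a stated method, "an exploratory comparison of treatment effects between the two randomization arms (sham first over real vs. real first over sham) will be performed". It does not define the treatment effect to be compared.

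**The concern.** In a sham-real/real-sham design, comparing the treatment effect between sequences is a comparison of periods. Differential carryover appears in the between-sequence difference of participants' totals, which the stated method does not examine. The purpose and the method in section 2.8 therefore do not match.

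This matters here because both effects are plausible:

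- **Period effect.** Everyone takes the same battery three times, and everyone receives eight further therapy sessions in period 2.
- **Carryover.** The Discussion (section 3) rests the rationale on strengthening plasticity. The washout is one week, and no battery is scheduled after it and before cycle 2.

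A positive check could cast doubt on a sound crossover estimate when only practice is at work. A null check could be reported as reassurance that it cannot give.

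**Working it through.** **Inputs from the article.** Two sequences (G1 sham-real, G2 real-sham); battery at T1, T2 and T3; final sample 60. The article gives no figure for this check. Its minimum of 48 is reproduced by the G*Power within-between interaction (f = 0.25, α = 0.0125, ε = 0.75) at a correlation of 0.5, which the article does not state; power is then 0.816. The point does not depend on that figure.

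**Assumed.** 30 per arm (1:1), SD 1, equal correlation ρ = 0.5 between visits, real-minus-sham effect d = 0.5 SD, no sham carryover, two-sided 0.05 unless stated. Rejection rates use the noncentral t.

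**1. What the check measures (end-of-period scores).** Let p be period 2 minus period 1 and L the carryover of real stimulation.
- G1, real − sham: T3 − T2 = d + p
- G2, real − sham: T2 − T3 = d − p − L
- G1 − G2 = 2p + L

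The effect d cancels, so the rates in step 2 do not depend on it. The crossover estimate is [(d + p) + (d − p − L)]/2 = d − L/2, a different combination.

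**2. How often the check is positive.** Var(T3 − T2) = 2(1 − ρ) = 1, so the SE of the contrast is √(1/30 + 1/30) = 0.258.

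| p | L | contrast 2p + L | contrast/SE | positive |
|---|---|---|---|---|
| 0.2 | 0 | 0.40 | 1.55 | 33% |
| 0.3 | 0 | 0.60 | 2.32 | 63% |
| 0 | 0.25 | 0.25 | 0.97 | 16% |
| 0 | 0.5 | 0.50 | 1.94 | 48% |
| 0.2 | 0.5 | 0.90 | 3.49 | 93% |
| −0.25 | 0.5 | 0 | 0 | 5% |

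Range: with ρ from 0.3 to 0.7 (SE 0.306 to 0.200), the first row runs from 25% to 50% and the second from 49% to 84%.

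**3. Other readings of the treatment effect.** Set T1 to zero, with period means p1 and p2.
- Change from the preceding visit: G1 − G2 = 2(p2 − 2p1) + L − d. Under a linear trend (p2 = 2p1), full carryover (L = d) gives 0 and is flagged in 5%. No carryover gives −0.5 SD. With SE √(3 × 2/30) = 0.447, that is flagged in about 20%.
- Real-phase change only: (p2 − p1 + d) − (p1 + d) = p2 − 2p1. L is absent.

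**4. What carryover does to the main estimate.** SE = 0.258/2 = 0.129. With L = 0.5 the estimate falls from 0.50 to 0.25 SD. Power falls from about 0.97 to 0.48 at α = 0.05, or from 0.90 to 0.27 at the sample-size α of 0.0125.

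**5. The alternatives.**
- T2+T3 totals, G2 − G1 = L, with no period term. Adjusted for T1, the residual variance is 3 − 1 = 2 and the SE is √(2 × 2/30) = 0.365. For L = 0.5, 0.5/0.365 = 1.37, so power is about 27%.
- First period, T2 real versus sham adjusted for T1: SE = √(0.75 × 2/30) = 0.224. The effect detectable with 80% power at 0.05 is (1.96 + 0.84) × 0.224 ≈ 0.63 SD.

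**The case against.** Five points can be made for the plan.

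- **The check is exploratory.** Section 2.8 labels it so, and nothing drops period 2 or changes the main analysis on its result. This stands and limits the consequence to interpretation.
- **The contrast is undefined, and a condensed article may leave detail to a fuller document.** The exact formula does depend on the definition. But section 2.8 fixes both purpose and method, and none of the three readings examined isolates carryover. The fault is in the method named, not in missing detail.
- **A reader might infer that the check mainly misses carryover.** On end-of-period scores with a practice gain, it does not: gain and beneficial carryover push the contrast the same way, and full carryover with a 0.2 SD gain is flagged in 93% of trials. The 5% case needs a period decline, contrary to the expected gain. The main defect is non-specificity. Misses come from low power, an opposite-sign period effect or a change-score definition.
- **A reader might infer that this is the only safeguard.** The document does not support that. The Group main effect in the planned ANOVA contains L and no period term, though its power is only about 12% for L = 0.5. The T1-to-T2 part of the interaction is the carryover-free first-period comparison. Section 2.4 also schedules EEG before session 9. None of these is named as a carryover analysis.
- **A reader might infer that the Figure 1 caption wrongly promises a post-washout battery.** It says "Neuropsychological assessment will be performed before and after each intervention" and labels the visits T1 to T3. T2 follows cycle 1 and precedes cycle 2, so the caption is compatible with section 2.3.

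**Conclusion.** The point holds as a should-fix. The algebra is exact for end-of-period scores: the planned check estimates 2p + L, while the bias in the crossover estimate is −L/2. A positive result may be practice alone, and a null result does not exclude carryover; at 0.25 SD of carryover with no period effect the check is positive in only about 16% of trials.

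The rates rest on assumed values (30 per arm, correlation 0.5, illustrative period and carryover sizes) and move with them. That the contrast is confounded with the period effect does not depend on those values. The document does not establish that carryover will occur or that the main analysis is invalid.

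**What to change.** In section 2.8:

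1. Replace the check with the between-sequence comparison of T2+T3 totals adjusted for T1, reported as an estimate with a confidence interval. State that it is not a gate, that its power is low (about 27% for 0.5 SD carryover under the assumptions above), and that it cannot be separated from a treatment-by-period interaction.
2. Name the first-period comparison (T2 real versus sham, adjusted for T1) as a carryover-free supportive analysis for each primary outcome, shown beside the crossover estimate. State its lower power: 80% for about 0.63 SD at 0.05 with 60 participants.
3. Optionally, compare the EEG already scheduled before session 9 with that before session 1, by sequence, as a post-washout check. It bears on EEG only, not on the clinical scores.

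The cost is analysis wording: no new visits, tests or participants. The change should be made before unblinding, so that the choice of estimate does not follow the results.
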